Appendix I: Visual Analogue Scale (VAS)

[figure not shown][figure not shown][figure not shown]

## Appendix J: CLINICAL DATA RECORD SHEET

### 1) Disabilities of the Arm, Shoulder and Hand (DASH) Outcome Measure

|                    | Initial Assessment
Date: | Reassessment
Date: |
|--------------------|-----------------------------|-----------------------|
| DASH Symptom Score |                             |                       |

### 2) LAM Assessment on Stages of Employment Readiness (LASER) Questionnaire

|             | Initial Assessment
Date: | Reassessment
Date: |
|-------------|-----------------------------|-----------------------|
| LASER Score |                             |                       |

### 3) Visual Analogue Scale (VAS)

|           | Initial Assessment
Date: | Reassessment
Date: |
|-----------|-----------------------------|-----------------------|
| VAS Score |                             |                       |

### 4) Grip Strength

|                       | Initial Assessment
Date: | Reassessment
Date: |
|-----------------------|-----------------------------|-----------------------|
| 1 st Trial |                             |                       |
| 2 nd Trial |                             |                       |
| 3 rd Trial |                             |                       |
| Average               |                             |                       |

### 5) Lateral Pinch Strength

|                       | Initial Assessment
Date: | Reassessment
Date: |
|-----------------------|-----------------------------|-----------------------|
| 1 st Trial |                             |                       |
| 2 nd Trial |                             |                       |
| 3 rd Trial |                             |                       |
| Average               |                             |                       |

### 6) Tripod Pinch Strength

|                       | Initial Assessment
Date: | Reassessment
Date: |
|-----------------------|-----------------------------|-----------------------|
| 1 st Trial |                             |                       |
| 2 nd Trial |                             |                       |
| 3 rd Trial |                             |                       |
| Average               |                             |                       |

7) Tip-to-tip Pinch Strength

|                       | Initial Assessment
Date: | Reassessment
Date: |
|-----------------------|-----------------------------|-----------------------|
| 1 st Trial |                             |                       |
| 2 nd Trial |                             |                       |
| 3 rd Trial |                             |                       |
| Average               |                             |                       |

8) Active Range of Motion – Forearm

|            | Initial Assessment
Date: | Reassessment
Date: |
|------------|-----------------------------|-----------------------|
| Supination |                             |                       |
| Pronation  |                             |                       |

9) Active Range of Motion – Wrist

|                  | Initial Assessment
Date: | Reassessment
Date: |
|------------------|-----------------------------|-----------------------|
| Extension        |                             |                       |
| Flexion          |                             |                       |
| Radial Deviation |                             |                       |
| Ulnar Deviation  |                             |                       |

10) Active Range of Motion – Hand

|               |              | Initial Assessment
Date: | Reassessment
Date: |
|---------------|--------------|-----------------------------|-----------------------|
| Thumb         | MCPJ Flexion |                             |                       |
|               | IPJ Flexion  |                             |                       |
| Index Finger  | MCPJ Flexion |                             |                       |
|               | PIPJ Flexion |                             |                       |
|               | DIPJ Flexion |                             |                       |
| Middle Finger | MCPJ Flexion |                             |                       |
|               | PIPJ Flexion |                             |                       |
|               | DIPJ Flexion |                             |                       |
| Ring Finger   | MCPJ Flexion |                             |                       |
|               | PIPJ Flexion |                             |                       |
|               | DIPJ Flexion |                             |                       |
| Little Finger | MCPJ Flexion |                             |                       |
|               | PIPJ Flexion |                             |                       |
|               | DIPJ Flexion |                             |                       |

### 11) Purdue Pegboard Test

Initial Assessment

Date:

|            | 1 st Trial | 2 nd Trial | 3 rd Trial | Average |
|------------|-----------------------|-----------------------|-----------------------|---------|
| Right Hand |                       |                       |                       |         |
| Left Hand  |                       |                       |                       |         |
| Both Hand  |                       |                       |                       |         |
| R + L + B  |                       |                       |                       |         |
| Assembly   |                       |                       |                       |         |

Reassessment

Date:

|            | 1 st Trial | 2 nd Trial | 3 rd Trial | Average |
|------------|-----------------------|-----------------------|-----------------------|---------|
| Right Hand |                       |                       |                       |         |
| Left Hand  |                       |                       |                       |         |
| Both Hand  |                       |                       |                       |         |
| R + L + B  |                       |                       |                       |         |
| Assembly   |                       |                       |                       |         |

### 12) Box and Block Test

Initial Assessment

Date:

|                                            | Right Hand | Left Hand |
|--------------------------------------------|------------|-----------|
| Number of Blocks Transferred in 60 Seconds |            |           |

Reassessment

Date:

|                                            | Right Hand | Left Hand |
|--------------------------------------------|------------|-----------|
| Number of Blocks Transferred in 60 Seconds |            |           |

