## **2.0 PROBLEM STATEMENT**

Most patients recovered from wrist fracture, particularly the distal radius fracture have some residual disability or pain. MacDermid et al. (2003) found that at one year following distal radius fracture, of 129 patients, there were still 46% of them experienced certain extent of difficulty with usual activities, ranging from very severe to mild. Although majority of recovery following a distal radius fracture occurred within six-months after conventional hand therapy regime, most of the patients can be expected

to still experience minimal pain and disability. Distal radius fracture cases can take up to few months and one or two years to achieve maximal functional improvement (Michlovitz et al., 2001). The residual disability or pain, along with the long functional recovery period following distal radius fracture may impact the socioeconomics of a person, family, and society significantly. With the advancement in rehabilitation technology, robotic intervention had shown positive outcomes in neurological rehabilitation programme for the past decades. However, there is a lacking of published evidence about the feasibility and effectiveness of robotic intervention in orthopaedic rehabilitation programme, especially in the field of hand therapy.

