### 3.6.6 Goniometer

Range of motion measurement will be done by using the goniometer. Active and passive ROM of the wrist and fingers of the fractured wrist will be assessed (Adams et al. 2003; Bland et al. 2008; Goldhahn et al. 2014; Waljee et al. 2016). Active ROM of the wrist joint, including wrist flexion, wrist extension, wrist radial deviation, wrist ulnar deviation will be assessed first, followed by AROM of the forearm rotation i.e. supination and pronation. Following AROM, passive ROM will be moved to end range in order to assess end feel. Passive ROM begins with the wrist flexion, wrist extension, wrist radial deviation, and wrist ulnar deviation. Following wrist motion, passive forearm rotation, i.e., supination and pronation will be tested to assess movement ability of proximal and distal radioulnar joints (Porretto-Loehrke et al. 2016). Active and passive ROM of the fingers' metacarpophalangeal joint (MCPJ), proximal interphalangeal joint (PIPJ), and distal interphalangeal joint (DIPJ) will be

assessed as well. The ROM measurements will be recorded using Clinical Data Record Sheet as shown in Appendix J.

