#### 3.6.7 Hand dynamometer and Pinch Gauge

Grip strength will be assessed with a Jamar hand dynamometer. Each participant's grip strength will be measured 3 times. Handle position 2 will be used as it is a recommended position for measuring grip strength by the American Society of Hand Therapists (Fess 1992). Meanwhile, lateral pinch strength, tripod pinch strength and tip-to-tip pinch strength will be measured by using the B&L Engineering Pinch Gauge (Mathiowetz et al. 2000). The grip and pinch strength measurements will be recorded using Clinical Data Record Sheet as shown in Appendix J.

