#### 3.6.8 Purdue Pegboard Test (PPT)

The Purdue Pegboard Test (PPT) is a standardized assessment consisting of four different subtests to determine user's level of dexterity. It is composed of a board with pins, collars, and washers. In the first three subtests, the subject has to place the maximum numbers of pins into holes in the pegboard with the dominant hand, the non-dominant hand, and then with both hands simultaneously within 30 seconds. In the fourth subtest the subject uses alternate hands in order to make assemblies consisting of pins, collars, and washers, in 60 seconds. A fifth score is given by summarizing the first three sub-tests (Shahar et al. 1998). The PPT was identified as one of the top three assessments of hand dexterity for health care professionals, due to its relatively higher reliability and validity and fewer confounding variables, such as age, gender, and handedness (Lindstrom-Hazel & Veenstra 2015). The Purdue Pegboard Test results will be recorded using Clinical Data Record Sheet as shown in Appendix J.

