#### 3.6.8 Box and Block Test (BBT)

The Box and Block Test (BBT) is a functional outcome measure that measures the gross manual dexterity and is commonly used across multiple clinical populations due to its benefits of ease and speed of implementation (Mathiowetz et al. 1985; Kontson et al. 2017). In the BBT, the subject is required to transfer

one hundred and fifty 2.5cm^3 wooden blocks that are placed in many different orientations on the side of the partition with the testing hand as fast as possible to another partition in one minute. A subject's score is equal to the number of these blocks transported over a 15.2-cm tall partition in one minute (Mathiowetz et al. 1985; Konston et al. 2017). The Box and Block Test had shown a high inter-rater and test-retest reliability with interclass correlations coefficients of 0.85 to 0.97 (Desrosiers et al. 1994; Platz et al. 2005; Canny et al. 2009). Mathiowetz et al. 1985 had published the normative data for the B&B Test for adults on the basis of 628 people without disabilities between ages 20 and 70+ years. The Box and Block Test results will be recorded using Clinical Data Record Sheet as shown in Appendix J.

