### **3.8 STATISTICAL ANALYSIS**

All data will be analysed using the IBM® SPSS® Statistics version 28. The study will use both descriptive and inferential statistics to analyse the data. Descriptive analysis for categorical data including gender, marital status, hand dominance, types of medical management and intervention, type of wrist fractures, educational level, employment status, and type of SOCSO compensation scheme will be expressed in frequency, percentage or/and proportion. Descriptive statistics for continuous data including age, DASH, pain, grip and pinch strength, wrist and finger ROM, hand dexterity, and work readiness scores will be expressed in mean, standard deviation, maximum, and minimum if the data is normally distributed or in median and inter-quartile range if the data is not normally distributed. The Shapiro-Wilks test will be used to test the normality of the continuous data.

The statistical analysis for each hypothesis will be tested using mixed model ANOVA by evaluating the mean differences in treatment outcomes between the groups at baseline and after 4 weeks of intervention.

Intention-to-treat (ITT) analysis will be used to analyze the difference between groups. ITT analysis, which aims to minimize bias and maintain random allocation of study participants (Gupta 2011), is suitable to be used when there are shedding participants. Its key idea is to analyse the group to which the participant belongs in that initial allocation, regardless of whether they completed the study or received the intended intervention.

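### Hypotheses 6 and 7 are tested without covariates although each hand is scored before randomisation; a week-4 ANCOVA on those baselines would gain precision

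*Combined protocol and SAP*

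**What the plan says.** Section 3.8 (Statistical Analysis) states that each hypothesis will be "tested using mixed model ANOVA", comparing the groups at baseline and after 4 weeks. No covariate is named.

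Hypothesis 6 (fine dexterity) rests on the Purdue Pegboard Test and hypothesis 7 (gross dexterity) on the Box and Block Test. The plan does not say which hand's score is the outcome for either:

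- Section 3.6.8 on Box and Block says that blocks are moved "with the testing hand as fast as possible to another partition in one minute", without identifying that hand. Appendix J item 12 has the columns "Right Hand | Left Hand" at both visits.
- Section 3.6.8 on Purdue describes pin placement "with the dominant hand, the non-dominant hand, and then with both hands simultaneously within 30 seconds", followed by an assembly task. Appendix J item 11 has rows for right, left, both hands, their sum, and assembly.

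Section 3.5, item g, has the allocation envelope handed over only after all baseline assessments, so the initial scores of both hands precede randomisation. Appendix B records hand dominance and has a free-text diagnosis entry, but no dedicated field for the fractured side. Sections 3.4.1 and 3.4.2 do not exclude bilateral fractures.

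Section 3.3 bases the sample size on a within-between interaction with f = 0.25, alpha 0.05 and 80% power. It reports 34 participants, or 38 after 10% dropout.

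**The concern.** With two visits, the group-by-time test is a comparison of mean change between groups. Change gives the baseline score a fixed weight of one, whereas ANCOVA estimates that weight. When the correlation between visits is below 1 and the variances are equal, ANCOVA has the smaller error variance. The injured hand's baseline is already collected, so the planned test gives up precision that costs nothing to recover.

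For a one-sided fracture, the sheets also hold the uninjured hand's baseline. The injured hand's baseline mixes the worker's usual dexterity with the deficit from the injury. That deficit may vary, because eligibility sets no limit on time since fracture, and section 2.0 says that "Distal radius fracture cases can take up to few months and one or two years to achieve maximal functional improvement". The other hand may therefore carry some information about week 4 that the injured hand's baseline lacks. As written, 3.8 gives it no role.

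What is at stake is power and interval width for hypotheses 6 and 7 in a trial of 38. The undefined hand also leaves the analyst to choose the outcome later.

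**Working it through.** **Inputs.** From section 3.3: f = 0.25, alpha 0.05, power 80%, N = 34, then 38. From section 3.8: two groups, two visits, no covariate. Assumed, because the documents do not give them: equal variances of 1 at both visits; visit correlation ρ; and the correlations of the uninjured hand's baseline with the injured hand at baseline (r0) and at week 4 (r1).

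**Step 1: reproduce the plan's figure.** For the within-between interaction, λ = f²·N·m/(1 − ρ), with 1 and N − 2 degrees of freedom and m = 2. At ρ = 0.5, λ = 0.0625 × 34 × 2/0.5 = 8.5 and power is 0.807; N = 32 gives 0.781. So 34 reproduces. Dropout: 34 × 1.10 = 37.4 and 34/0.90 = 37.8, both rounding up to 38.

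**Step 2: the same test as a test on change.** Variance of change V = 2(1 − ρ) = 1.00. The effect f = 0.25 is a difference in change of 4f = 1.0 SD. Then λ = 1.0² × 34/(4 × 1.00) = 8.5, as in step 1.

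**Step 3: ANCOVA on the injured hand's baseline.** V = 1 − ρ² = 0.75, which is 25% lower. Power at N = 34 is 0.903, and 80% power needs N = 26. In general the ratio to the planned test is (1 − ρ²)/[2(1 − ρ)] = (1 + ρ)/2: 0.65 at ρ = 0.3, 0.75 at 0.5, 0.85 at 0.7.

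**Step 4: add the uninjured hand's baseline to that ANCOVA.** V = 1 − (ρ² + r1² − 2·ρ·r0·r1)/(1 − r0²). At r0 = r1 = 0.5: 1 − (0.25 + 0.25 − 0.25)/0.75 = 0.667, and 1 − 0.667/0.75 = 11%. With ρ = 0.5 throughout:

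| r0 / r1 | V | Reduction beyond 0.75 | Power at N = 34 | N for 80% |
|---|---|---|---|---|
| 0.1 / 0.1 | 0.747 | 0.3% | 0.904 | 26 |
| 0.3 / 0.3 | 0.725 | 3.3% | 0.912 | 26 |
| 0.5 / 0.5 | 0.667 | 11% | 0.932 | 24 |
| 0.3 / 0.5 | 0.615 | 18% | 0.949 | 22 |
| 0.3 / 0.7 | 0.418 | 44% | 0.992 | 16 |

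The gain vanishes where r1 = ρ·r0. With 34 − 2 − 2 = 30 residual degrees of freedom, the extra covariate costs about 1/30, or 3%. At 0.3 / 0.3 gain and cost roughly cancel.

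**Step 5: add the uninjured hand to the planned test instead.** V = 2(1 − ρ) − (r1 − r0)². If r0 = r1, V stays at 1.00 (power 0.806 against 0.807). At 0.3 / 0.5, V = 0.96 and power is 0.822. At 0.3 / 0.7, V = 0.84 and power is 0.869.

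**The case against.** The strongest objection is that the planned test already removes stable differences between workers, because a constant personal level cancels in the change score. A reader might infer that such differences stay in the error term because the uninjured hand is unused. Step 5 shows otherwise: the uninjured hand adds nothing to the planned test if it correlates equally with both visits. This stands. The case for the second covariate holds only within a week-4 ANCOVA, or if the uninjured hand predicts week 4 better than baseline.

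It is also fair that most of the dependable gain needs only the injured hand's baseline, and that the size of the rest is assumed. One way to fix it is to let a stable personal level make up a share s of the variance, common to both hands. Then V = 1 − 0.25/(1 − s × reliability). With s from 0.25 to 0.50 and the 0.85 to 0.97 reliability quoted for Box and Block, V runs from 0.683 to 0.515, a reduction of 9% to 31%. The arithmetic is right, but it allows no difference between hands, such as dominance. At s = 0.50 it implies a correlation between hands of √(0.50 × 0.85) = 0.65 to √(0.50 × 0.97) = 0.70, above the 0.5 assumed between visits of the same hand. The documents support neither.

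A reader might go further and ask for the uninjured side to be measured for grip, pinch and motion. The documents do not support that request. Section 3.6.6 makes a stated choice: "Active and passive ROM of the wrist and fingers of the fractured wrist will be assessed". For grip, section 3.6.7 says only that "grip strength will be measured 3 times". New measurements would be needed, and no gain can be computed for those instruments. Nor do the documents describe the uninjured hand as the best measure of a worker's normal level.

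**Conclusion.** The point holds as a missed gain in efficiency for hypotheses 6 and 7. A reader might infer that the planned ANOVA is biased or invalid without the covariate; it is not, since randomisation protects the comparison either way.

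The dependable part is the move from change to a week-4 ANCOVA on the injured hand's baseline: 25% lower error variance at ρ = 0.5, before the small cost of one degree of freedom. That value is inferred from N = 34, not stated; at ρ between 0.3 and 0.7 the reduction is 35% to 15%. The uninjured hand's baseline is a reasonable second covariate, worth about 0.3% to 44% more over the pairs tried and 11% at 0.5 / 0.5, against about 3% in cost. Its true value is unknown.

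The gap that has to be closed in any case is that the plan names no outcome hand and has no dedicated record of the fractured side.

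**What to change.** In section 3.8, before any outcome data are analysed:

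1. Name the injured hand's week-4 Box and Block score and the injured hand's week-4 single-hand Purdue score as the outcomes for hypotheses 7 and 6. Treat the other Purdue scores (both hands, sum, assembly) as supporting results.
2. Analyse each by ANCOVA with group, the injured hand's baseline, and the uninjured hand's baseline as a second pre-specified covariate.
3. State that the uninjured hand's week-4 value will not be a covariate, because it is measured after randomisation.
4. State how participants with bilateral fractures are handled, since they have no uninjured hand.

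In Appendix B or J, add a field for the fractured side, and complete it from the medical record for anyone already enrolled.

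The cost is a few sentences, one recorded item per participant, and one degree of freedom per covariate. No further performance test is needed, and the sheets for grip, pinch and motion can stay as they are.
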